In recent decades, the application of task fMRI makes it possible to provide evidence of human’s cerebral and behavioral response towards acupuncture stimulation [33–35]. Hence, in order to testify the hypothesis that either acupuncture with GB34 or EX-LE6 is superior in alleviating GSD patients’ symptoms compared to acupuncture with the non-acupoint, a fatty-food-cue task during MRI scan is designed to induce pain and accompanied discomforts of GSD patients and then the GSD patients’ behavioral and neural response change among all three groups before and after acupuncture will be compared. Therefore, the primary objective is to testify the therapeutic effect of acupuncture with GB34 and EX-LE6 in comparison to the non-acupoint and then further explore the superior effect between acupuncture with GB34 and EX-LE6 and finally investigate the potential central mechanism underlying acupuncture with GB34 and EX-LE6.

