### Sample size

According to our previous study, the Numeric Rating Scale (NRS) of GSD patients decreased by 2.4 points after acupuncture and by 0.85 points after non-acupoint acupuncture. In this study, we anticipate a reduction of NRS score by 2.4 points after acupuncture with GB34 or EX-LE6, and we anticipate a reduction by 0.85 points after acupuncture with non-acupoint. With α = 0.05, 1 β = 0.8, and a standard deviation of 2, we need at least 81 participants in total. Considering a 10% dropout, the sample size of 30 in each group, with a total of 90 participants, would be required in this trial. And 30 patients in each group have a stable statistical power for brain functional network analysis [39].

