### Statistical analysis

#### Clinical data analysis

The clinical data will be statistically analyzed by SPSS 22.0 software (IBM SPSS Statistics, IBM Corp, Somers, New York). Skewed data distribution will be normalized. Means, standard deviations, and 95% confidence intervals (CIs) will be computed to describe continuous variables. Since only one session of acupuncture will be conducted in our study, the per-protocol (PP) analysis will be used, and the subjects with missing data will be excluded. The reasons for missing data should be recorded in detail.

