#### Clinical outcome analysis

Comparison of NRS scores between four timepoints among three groups will be made using a repeated-measures ANOVA. Further, the planned contrast of changed NRS scores (before vs. after acupuncture; before vs. after fatty-food cues) will be conducted with a one-sided exact test for which *p* < 0.05 is considered significant.

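### The planned contrasts on the primary outcome (NRS) are tested one-sided at 0.05 with no stated direction or reason, a looser criterion than the sample size of 81 implies

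*Protocol article*

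**What the plan says.** The NRS is the primary outcome, rated at four timepoints (Primary outcome measurement). Under Clinical outcome analysis, a repeated-measures ANOVA comes first. Planned contrasts of NRS change follow, across acupuncture and across the fatty-food cues, and each "will be conducted with a one-sided exact test" with p < 0.05 counted as significant. The section does not say which tail applies, why one tail is enough, which groups are compared, or whether the contrasts are within or between groups.

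The Sample size section sets the level as "With α = 0.05" without sidedness. Its effect assumption is "we anticipate a reduction of NRS score by 2.4 points after acupuncture with GB34 or EX-LE6", against a reduction of 0.85 points for the non-acupoint. Power is 0.8, and the result is "a standard deviation of 2, we need at least 81 participants in total", raised to 90 for 10% dropout.

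The Abstract assigns GB34 versus EX-LE6 to a post hoc t-test and gives no sidedness for it.

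**The concern.** The sample size and the analysis should use the same error rate for the same question. If 81 comes from a two-sided 0.05 calculation and the contrasts are then tested one-sided at 0.05, the threshold for a favourable result is looser than the one the trial was sized for, and nothing in the text explains the change.

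A one-sided test also needs its direction fixed beforehand. Here one undirected rule serves two contrasts that can point opposite ways. Pain is expected to fall across acupuncture, while the Background says that the cue task is designed to induce pain. For the cue contrast the relevant tail could be a rise in pain within a group or a smaller rise in an active group than in the control. The text leaves this open, so the tail could be settled after the data are seen. At stake is the meaning of a significant result on the primary outcome.

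**Working it through.** **Inputs** (Sample size section): reduction 2.4 with GB34 or EX-LE6, 0.85 with the non-acupoint, so δ = 2.4 − 0.85 = 1.55; SD σ = 2; alpha 0.05; power 0.80; dropout 10%. Allocation is 1:1:1 (Randomization section).

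**Formula** (two means, normal approximation): n per group = 2σ²(z_α + z_0.80)² / δ², with z_0.80 = 0.8416, 2σ² = 8 and δ² = 2.4025.

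**Reproducing the plan's figure**
- Two-sided 0.05: 8 × (1.9600 + 0.8416)² / 2.4025 = 26.14, rounded up to 27 per group; 3 × 27 = 81; 81 / 0.9 = 90. Both stated totals match exactly.
- One-sided 0.05: 8 × (1.6449 + 0.8416)² / 2.4025 = 20.59, rounded up to 21 per group; 3 × 21 = 63; 63 / 0.9 = 70. Neither total matches.
- One-sided 0.025 has the same critical value as two-sided 0.05, so it also gives 81.

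**Other routes tried, total before dropout**
- Two-sample t-test: 84 two-sided, 66 one-sided.
- One-way ANOVA F-test with means 2.4, 2.4 and 0.85: 78 (26 per group).
- Both active arms pooled 2:1 against control: 60 two-sided, 48 one-sided.
- One-sided 0.05 at 90% power: 87.

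None of these gives 81.

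**Error rate.** A two-sided 0.05 test allows 0.05 / 2 = 2.5% in the favourable direction. A one-sided 0.05 test pointed that way allows 5%, which is twice as much per contrast.

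**Illustration in NRS points.** Assume a between-group t-test with 27 per group and SD 2, which the article does not specify. The standard error is 2 × √(2/27) = 0.544, with 52 degrees of freedom.
- One-sided 0.05: critical difference 1.675 × 0.544 = 0.91.
- Two-sided 0.05: critical difference 2.007 × 0.544 = 1.09.

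**Power at δ = 1.55**

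| Per group | Two-sided 0.05, normal | Two-sided 0.05, t | One-sided 0.05, normal | One-sided 0.05, t |
|---|---|---|---|---|
| 27 | 81.3% | 79.8% | 88.5% | 87.8% |
| 30 | 85.1% | 83.9% | 91.3% | 90.7% |

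The two-sided test has essentially the planned power at the planned N, so one-sided testing is not needed to reach it.

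**The case against.** The plan has a fair defence on several counts.

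- **Sidedness of the sizing is inferred.** The Sample size section does not state it. One-sided 0.05 split equally over two comparisons with the control would be one-sided 0.025 each and would also give 81. The article describes no such split, and the contrasts are written at an undivided 0.05.
- **There is a directional hypothesis against control.** In the Background, "either acupuncture with GB34 or EX-LE6 is superior" goes on to name the non-acupoint as comparator. That gives some rationale for one tail in an active-versus-control contrast. It does not justify a level twice that of the sizing, and it does not fix the tail for the cue contrast.
- **The ANOVA comes first.** Its F-test has no direction, and the article does not say which result carries the primary claim. So it cannot be said that the primary claim as a whole rests on the looser level. The point is confined to the planned contrasts.

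Two stronger readings are tempting and are not supported.

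- **GB34 versus EX-LE6.** A reader might infer that this comparison, which has no predicted direction and the same assumed reduction of 2.4 in both arms, is also tested one-sided. Choosing the side afterwards would then give 5% + 5% = 10% error. But the contrasts are defined by timepoint and name no pair of groups, and the Abstract gives this comparison a post hoc t-test. The 10% is conditional on a procedure the article does not state.
- **Conflict with reported intervals.** A reader might infer that a significant contrast could stand beside the trial's own 95% interval for the difference including zero. Under Clinical data analysis, "95% confidence intervals (CIs) will be computed" refers to describing continuous variables. No interval for a between-group difference is promised.

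**Conclusion.** The concern holds in this limited form. The planned NRS contrasts use a one-sided 0.05 test with no direction or justification, while the stated 81 and 90 match two-sided 0.05 (or one-sided 0.025) and not one-sided 0.05. Measured against what the sizing implies, the nominal false-positive rate in the favourable direction is 5% instead of 2.5% for each contrast.

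This rests on reading sidedness from the arithmetic, which fits both stated totals exactly. The band of 0.91 to 1.09 points rests further on a between-group t-test, 27 per group and SD 2. An exact test or a within-group contrast would have a different band. The mismatch does not leave the trial underpowered, because the one-sided test has more power at the same N.

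**What to change.** - **Clinical outcome analysis:** replace the one-sided test with two-sided tests at p < 0.05 for all planned NRS contrasts, and name the groups each contrast compares.
- **Post hoc comparison of GB34 with EX-LE6:** say that the t-test is two-sided.
- **Sample size:** state that alpha is two-sided 0.05.

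The planned N of 90 does not change. The only cost is a stricter threshold for the contrasts. The article reports six participants recruited at the time of writing, so on that status the change could be recorded well before the outcome data could influence it.

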#### In-scanner behavioral rating analysis

For the 11-Likert scale scores obtained during the task, we employ a 3 × 2 × 2 repeated-measures ANOVA with the group (group A, group B, group C), timepoint (pre-acupuncture, post-acupuncture), and condition (high-fatty food pictures, low-fatty food pictures). Post hoc analyses will be conducted using Tukey post hoc or Bonferroni comparisons. And the post hoc significant differences (p < 0.05) will be followed up with t-tests. The data will be considered statistically significant with a level of 0.05.

#### Neuroimaging data analysis

All image preprocessing and general linear modeling will be done using SPM12 software (SPM12, Wellcome Department of Imaging Neuroscience, London, UK; www.fil.ion.ucl.ac.uk/spm/) performing on MATLAB 8.6 (Mathworks, Inc., Natick, MA, USA). Data preprocessing will include the first 5 timepoints discarding for magnetic saturation effects, slice timing, head-motion correction, spatial normalization in Montreal Neurological Institute (MNI) space resampled at 3 mm × 3 mm × 3 mm voxel size, filtering, and spatial smoothing using an 8-mm FWHM Gaussian kernel.

After preprocessing, the general linear model (GLM) will be used to model task-related effects. The inter-block interval serves as an implicit baseline. The two task conditions (high- and low-fat food), the 10-s 11-Likert scale rating period, and six head-motion parameters to control motion-related artifacts will be designed for the first-level design matrix. The following contrast (high-fat food cues > low-fat food cues), for each subject and for each session (before and after acupuncture treatment), will be then used for the second-level group analysis.

Furthermore, for correlation analyses, a Spearman correlation analysis will be performed to investigate a possible correlation between neural changes and clinical data.

## Discussion

To explore the superior effect between acupuncture with GB34 and EX-LE6 on reliving GSD patients’ behavioral and neural response and the underlying central mechanism, the RCT is designed with a fatty-food-cue task to induce patients’ behavioral and neural reactivity. To our knowledge, this will be the first parallel, randomized study of acupuncture in combination with clinical questionnaire evaluations and task-fMRI among digestive diseases. The results are based on the NRS outcome and objective outcomes from the fMRI study, which may help provide more convincing evidence that immediate acupuncture is effective for alleviating pain and accompanied symptoms such as aversion to fatty food, vomiting, nausea, etc. for GSD patients.

The close relationship between acupoints and viscera is the basis of the bi-directional therapeutic effect of acupuncture for viscera disease [50]. In the theory of traditional Chinese medicine, the selection of the acupoint is crucial to the curative effect. Although many studies have demonstrated verum acupoint superior to non-acupoint in alleviating pain and suffering [51, 52], the acupoint specificity remains controversial. GB34 locates in the gallbladder meridian, which is particularly effective for gallbladder disease treatment. Moreover, it has been concluded that the hypothalamus-limbic system was significantly modulated by acupuncture at GB34 rather than at non-acupoint [53]. Hence, in comparison to the non-acupoint, this trial aims to firstly explore the superior effect between acupuncture with GB34 and EX-LE6 on GSD patients by observing their behavioral and neural response change to fatty-food cue and then to investigate the underlying central mechanism. This may have important implications for the effect of acupuncture in improving biliary and gastrointestinal symptoms.

On the condition of deficient motility of the biliary system with stones stuck in the gallbladder and cystic duct, bile acid transmission is blocked and the normal digestion of fat in the gastrointestinal system is affected [54]. Acupuncture, especially on the acupoint GB34, has been demonstrated not only for biliary colic relief, but also for having regulating effect on the biliary system [24–28]. However, the underlying central mechanism has never been investigated to date. Therefore, a fatty-food-cue task during an MRI scan is designed to induce pain and accompanied discomforts of GSD patients to investigate the immediate effect of acupuncture on the brain response and its association with patients’ behavior.

To improve the reliability and repeatability of study results, a strict quality control is indispensable. In this study, quality control will be strengthened focus on baseline consistency, strict task design, and fMRI scan, as well as the trained acupuncture manipulation. Participants will be screened strictly according to inclusion and exclusion criteria. The selected food pictures are edited with a unified standard to ensure the identification and visual homogeneity. And prior to the food-cue task, these pictures would be evaluated using online questionnaires. All scans are performed by the same scanner and operator. The same experienced acupuncturists with standard operation procedure are in charge of acupuncture treatment. There are still some limitations that should be noted in this study. Firstly, the one-time acupuncture treatment may be insufficient to achieve a measurable response. Prolonged treatment periods should be considered in the future study. Secondly, as the unique nature of acupuncture and many patients in China are familiar with *deqi* sensation, it is impossible to completely blind all participants. Another limitation is that the primary and secondary outcome measures in this study are self-rating scale, where the outcome assessors may not be able to blind to group allocation and intervention.

In conclusion, the results of this study will allow to observe the superior effect between acupuncture with GB34 and EX-LE6 on alleviating GSD patients’ symptoms. In addition, the potential central mechanism underlying acupuncture with GB34 and EX-LE6 will be further investigated.

## Trial status

This trial was registered on 3 July 2020 (registration number: ChiCTR2000034432; version number: 2.1; version date: 1 January 2021). This trial is still recruiting patients now. This trial is currently in the stage of recruiting patients. The first participant was included on 26 August 2020. To date, 6 participants have been recruited. And the trial is expected to end on 10 December 2021.

## Data Availability

Not applicable. This is only a study protocol and as such no unpublished data are available.

## Abbreviations

GSD: Gallbladder stone disease
BC: Biliary colic
CCK: Cholecystokinin
GB34: Yanglingquan
EX-LE6: Dannang
fMRI: Functional magnetic resonance imaging
RCTs: Randomized controlled trials
SPIRIT: The Standard Protocol Items: Recommendations for Intervention Trials
EASL: The European Association for the Study of the Liver
NSAIDs: Nonsteroidal anti-inflammatory drugs
WBCs: White blood cells
SAS: The Zung Self-Rating Anxiety Scale
SDS: The Zung Self-Rating Depression Scale
CRFs: Case report forms
ST34: Zusanli
TR: Repetition time
TE: Echo time
FOV: Field of view
BOLD: Blood-oxygen-level dependent
GRE-EPI: Gradient-Recalled Echo-Planar Imaging
NRS: The Numeric Rating Scale
SF-12: The 12-item Short Form Health Survey
SF-36: The 36-item Short Form Survey
C-MASS: Chinese version of modified Massachusetts General Hospital Acupuncture Sensation Scale
CIs: Confidence intervals
ANOVA: One-way analysis of variance
MNI: Montreal Neurological Institute
GLM: General linear model
